## Abstract

**Background:**

This study aims for health gain and cost reduction in the care for people with long-term non-psychotic psychiatric disorders. Present care for this population has a limited evidence base, is often open ended, little effective, and expensive. Recent epidemiological data shows that 43.5% of the Dutch are affected by mental illness during their life. About 80% of all patients receiving mental health services (MHS) have one or more non-psychotic disorders. Particularly for this group, long-term treatment and care is poorly developed. Care As Usual (CAU) currently is a form of low-structured treatment/care. Interpersonal Community Psychiatric Treatment (ICPT) is a structured treatment for people with long-term, non-psychotic disorders, developed together with patients, professionals, and experts. ICPT uses a number of evidence-based techniques and was positively evaluated in a controlled pilot study.

**Methods/Design:**

Multi-centre cluster-randomized clinical trial: 36 professionals will be randomly allocated to either ICPT or CAU for an intervention period of 12 months, and a follow-up of 6 months. 180 Patients between 18–65 years of age will be included, who have been diagnosed with a non-psychotic psychiatric disorder (depressive, anxiety, personality or substance abuse disorder), have long-term (>2 years) or high care use (>1 outpatient contact per week or >2 crisis contacts per year or >1 inpatient admission per year), and who receive treatment in a specialized mental health care setting. The primary outcome variable is quality of life; secondary outcomes are costs, recovery, general mental health, therapeutic alliance, professional-perceived difficulty of patient, care needs and social contacts.

**Discussion:**

No RCT, nor cost-effectiveness study, has been conducted on ICPT so far. The empirical base for current CAU is weak, if not absent. This study will fill this void, and generate data needed to improve daily mental health care.

**Trial registration:**

Netherlands Trial Register (NTR): 3988. Registered 13th of May 2013.

## Background

In the Netherlands, as in many other developed countries, many people suffer from psychiatric disorders during their life. Recent epidemiological data show that 43.5% of the Dutch are affected by some form of mental illness during their life [1]. Depression (20.1%), anxiety (19.6%), and substance abuse (19.1%) have the highest lifetime prevalence: the first two appear in the Dutch top-4 of diseases with the highest disease burden [2]. Comorbidity with personality disorders, which have a prevalence of 9.1% in western society [3], results in poorer social functioning and limited recovery.

About 80% of all patients receiving mental health services (MHS) have one or more of the aforementioned non-psychotic disorders [4]. Between 16-18% of these patients do not respond well to short-term treatment (i.e. <15 contacts or <1 year treatment) and end up in long-term care [5,6]. Long-term treatment and care are poorly developed: 50-70% of these patients receive a form of long-term supportive treatment/counselling/care, which we refer to as care as usual (CAU). CAU currently is a low-structured treatment/care: biweekly contacts with a nurse, social worker or occupational therapist, in which daily issues are discussed [7]. The other 30-50% of the patients receive long-term psychotherapy – of which many are eventually referred to long-term CAU. Thus, often when short-term treatment has proven ineffective, long-term care with a poor focus is the only alternative. Specific treatments for subgroups, e.g. patients with chronic depression, exist [8] but are not widely implemented. As a result, large numbers of people yearly receive a non-descript form of long-term care. The lack of direction in CAU results in: 1) very long-term care (e.g. up to 10 years [9]) and 2) high care use. Several studies show that 10-30% of chronic patients use 50-80% of mental health care’s resources [10]. These resources include (intensive) ambulatory care, as well as services such as crisis intervention outside office hours, ambulance transport, and admissions to hospitals, and ER/ casualty-departments. Long-term and intensive care use is highly correlated with the perceived patient ‘difficulty’ [11,12]. When a patient is labeled ‘difficult’ quality of care often becomes low [13]. For patients this results in lower quality of life, more symptoms, and even higher care use [14].

For those patients who receive CAU, we developed Interpersonal Community Psychiatric Treatment (ICPT). Feasibility and preliminary effectiveness of ICPT were evaluated in a controlled pilot-study [9], in which ICPT was more successful than CAU on a number of outcome variables. Patients gained quality of life and social contacts, and used fewer health care services. Professionals (e.g. community psychiatric nurses and nurse specialists) valued the therapeutic alliance more positively, and experienced both patients and patient care as less ‘difficult’. ICPT is not yet standard care but is being used on a small scale. Given the positive outcomes in a group of patients with complex needs, ICPT seems a promising intervention. Yet data from RCTs on the (cost) effectiveness of ICPT is not available.

### Target population

The intervention in this study aims at a broad group of patients in terms of psychiatric diagnosis (non-psychotic disorders in several combinations) and in terms of demographic characteristics (although women, and persons with a lower socio-economic status are overrepresented), but a specific group in terms of care use (long-term and intensive). The severity of the disorder may account for the long duration of care, yet in psychiatric care people may also become accustomed to using services. Some studies highlight such iatrogenic dependency [15], and show very high service use of non-psychotic patients across health and social services [10]. We specifically aim at this group of patients, who have serious mental illnesses, but who may also have become accustomed to long term or high care use. These patients may be perceived as ‘difficult’ [16] and difficult-to-place, and be passed around by services [11]. They may get lost in the system, since they neither fit in long-term care programs (mostly aimed at patients with psychotic disorders), nor in short-term therapy (mostly aimed at patients with singular non-psychotic disorders, who respond well to medication and/or psychotherapy). Instead of keeping on ‘pampering and dithering’ we offer this group a generic program that aims at improving quality of life while decreasing costs.

### Research aim and hypotheses

This study aims at comparing the effectiveness and costs of ICPT in the treatment of people with long-term non-psychotic mental illness to CAU.

Based on a previous controlled pilot study of 36 patients [9], our main hypothesis is that ICPT is more effective in improving patients’ quality of life and social networks than CAU. Further, we hypothesize that ICPT is more effective in preventing or decreasing professionals’ perception of patients as ‘difficult’, resulting in higher quality of care than CAU and that ICPT is more effective in discharging patients to a lower level of care (i.e. general mental health care instead of specialized mental health care) and more cost-effective in reaching aforementioned clinical goals than CAU.

## Methods/Design

### Design

Multi-centre cluster-randomized clinical trial: participating professionals will be randomly allocated to either ICPT or CAU for an intervention period of 12 months, and a follow-up of 6 months (total 18 months). Participating patients will receive ICPT or CAU during 12 months. There is a measurement at baseline, an intermediate measurement (6 months after baseline), after the intervention period (12 months after baseline), and a follow-up measurement (6 months after end of intervention, 18 months after baseline).

### Randomization

The professionals (clusters) will be randomized the intervention (ICPT) or the control group (CAU) using randomized stratification by an independent statistician. The allocation sequences will be generated with an automated algorithm by a statistician independent from the recruiter of the professionals using a random sequence generation.

### Inclusion and exclusion criteria

Patients between 18–65 years of age with a presence of a non-psychotic psychiatric disorder such as depressive, anxiety and/or personality disorder and/or substance abuse and long-term treatment (>2 years) or high care use (>1 outpatient contact per week or >2 crisis contacts per year or >1 inpatient admission per year) in secondary mental health services will be included. Patients with a psychotic, bipolar I or cognitive disorder (e.g. dementia) and a lack of skill in understanding of, or communication in Dutch language are excluded.

Professionals who have an individual caseload of > 5 patients with a non-psychotic disorder, who are willing to be randomized to either CAU or the experimental ICPT-condition and have not expressed intention to leave the present service between now and 12 months are included. Refer to Figure 1 Participant flowchart for details.

**Figure 1 Fig1:**
[figure not shown]
Participant Flow Chart.

### Sample size calculation

This study’s sample size calculation is based on the primary outcome variable, quality of life as measured with the Manchester Short Assessment of Quality of Life (MANSA), for which we found an effect size of 0.3 in our pilot study [17]. In a patient group in which quality of life is difficult to improve, an effect size of 0.3 signifies clinically meaningful progress. Furthermore we assumed a conservative Intra Cluster Correlation of 0.10 for clustering of patients, based on the scarce literature on the correlation between long-term psychiatric patients within one professional [17]. The correlation between baseline and follow-up measurement, also from our pilot study, was set at 0.5 and 0.8 for cluster and subject level, respectively. With an alpha of 0.05, and a power of 0.80, 36 clusters (professionals) of 5 participants (patients) each are required (total of 36 professionals and 180 patients needed for the analysis).

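### The stated 80% power for 36 clusters of 5 does not follow from the protocol's own inputs under the standard baseline-adjusted formula with one follow-up, which gives about 65%

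*Protocol article*

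**What the plan says.** The Sample size calculation section bases the trial's size on the MANSA quality-of-life score. It takes the target effect from the pilot ("we found an effect size of 0.3 in our pilot study") and treats that effect as clinically meaningful. For clustering, "we assumed a conservative Intra Cluster Correlation of 0.10 for clustering of patients". The baseline to follow-up correlation, also from the pilot, "was set at 0.5 and 0.8 for cluster and subject level, respectively". The conclusion is "With an alpha of 0.05, and a power of 0.80, 36 clusters (professionals) of 5 participants (patients) each are required", with a "total of 36 professionals and 180 patients needed for the analysis".

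The section does not state whether the test is one- or two-sided, the allocation ratio, the formula, or how many follow-up measurements the calculation used. It speaks of the correlation between baseline and follow-up measurement in the singular. The Design section places follow-ups at 6, 12 and 18 months (T1 to T3). The Statistical analyses section plans a linear mixed model for repeated measurements, adjusted for characteristics such as quality of life, and names no primary visit.

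**The concern.** The effect size, the intra-cluster correlation, both correlations, the cluster size, alpha and power are all printed, so the result can be checked with little more than a calculator. The obvious check gives a clearly larger requirement than 36 clusters. The trial's size rests on this figure, and a null result will be read against it. If the primary contrast turns out to be at a single visit, a reader told that power is 80% would overestimate how well the trial could detect an effect of 0.3.

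**Working it through.** **Inputs (Sample size calculation section):** d = 0.3 in total-SD units; ICC = 0.10; cluster-level correlation 0.5; subject-level correlation 0.8; m = 5 patients per cluster; alpha 0.05; power 0.80; 36 clusters, 180 patients analysed. **Assumed:** two-sided test, 18 clusters (90 patients) per arm, one follow-up, no losses.

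**Step 1. Individually randomised, unadjusted.** n per arm = 2(1.96 + 0.8416)² / 0.3² = 174.4.

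**Step 2. Clustering.** Design effect = 1 + (5 − 1)(0.10) = 1.4.

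**Step 3. Correlation of cluster means between baseline and follow-up.** r = [m·ICC·0.5 + (1 − ICC)·0.8] / 1.4 = (0.25 + 0.72) / 1.4 = 0.693, so 1 − r² = 0.520.

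**Step 4. Combined factor.** 1.4 × 0.520 = 0.728.

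**Step 5. Requirement for 80% power.** 174.4 × 0.728 = 127 per arm; 127 / 5 = 25.4 clusters per arm; 50.8 in total, so 51, or 52 (260 patients) with equal arms.

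**Step 6. Power at 36 × 5.** SE = √(2 × 0.728 / 90) = 0.127; 0.3 / 0.127 = 2.36; power = Φ(2.36 − 1.96) = 0.655. With a non-central t on 34 df it is 0.63. The effect detectable with 80% power is 2.80 × 0.127 = 0.36 (0.37 with t).

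**Other readings of the stated inputs, one follow-up:**

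| Reading | Power at 36 × 5 | Clusters for 80% |
|---|---|---|
| Separate baseline adjustment at each level, two-sided | 67% | 48.8 |
| 0.8 read as the subject's total correlation, two-sided | 68% | 47.8 |
| The two correlations swapped, two-sided | 57% | 61.7 |
| Change score, two-sided | 58% | 60.0 |
| Follow-up score only, two-sided | 40% | 97.7 |
| Formula of steps 1 to 6, one-sided | 76% | 40 |

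**Routes that do arrive at 36 (18 per arm), each needing something the text does not state:**

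- 0.8 at both levels, leaving out the 0.5: factor 1.4 × 0.36 = 0.504; 17.6 clusters per arm; power 0.81.
- No clustering inflation: factor 0.520; 18.1 clusters per arm, which is 18 only if rounded down; power 0.80.
- Mean of two follow-ups, with the same correlations between all visits: factor 1.4[(1 + 0.693)/2 − 0.480] = 0.513; 17.9 clusters per arm; power 0.80.
- One-sided test, separate adjustment at each level, and 0.8 read as the total correlation. The within-cluster correlation is then (0.8 − 0.05)/0.9 = 0.833 and the factor is 0.5(1 − 0.25) + 0.9(1 − 0.694) = 0.65. One-sided unadjusted n per arm = 2(1.645 + 0.8416)²/0.09 = 137.4; 137.4 × 0.65 / 5 = 17.9 clusters per arm; power 0.80.

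**If the treatment effect is averaged over T1 to T3** (same correlations between all visits, no losses): factor 1.4[(1 + 2 × 0.693)/3 − 0.480] = 0.441; SE = √(2 × 0.441/90) = 0.099; power 0.86, or 0.84 with t. This holds if the effect averages 0.3 over the visits. If it were 0.15 at T1 and 0.3 afterwards, the mean is 0.25 and power falls to 0.71 (0.69 with t).

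**The case against.** Three things can be said for the protocol.

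First, not every input is given. Sidedness, allocation, formula and number of follow-ups are absent, and an article may leave the formula and software to a fuller document. That is fair, and it is why the figures above are conditional. It does not restore the printed result: for a single follow-up, neither the two-sided nor the one-sided version of the standard formula reaches 80% with 36 clusters.

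Second, a reader might infer that no combination of the printed numbers can yield 36. The documents do not support that. The last route listed in the check keeps every stated value and gives 35.7 clusters, and the article's hypothesis is directional. However, that route stacks three unstated choices, and nothing shows that it was used. Which route was taken, if any, is guesswork.

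Third, and strongest, the planned analysis is a repeated-measures mixed model with three follow-ups. A reader might infer from the 65% that the trial as designed has a 35% chance of missing the effect. That goes too far: the 35% belongs to a single-visit contrast, and no visit is named as primary. An averaged contrast could exceed 80%. But the sample size paragraph mentions no averaging and gives no correlation between follow-ups, and the analysis section does not define the effect as a mean over visits. The printed 80% therefore cannot be credited to averaging as the text stands.

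**Conclusion.** The concern stands in a conditional form. With the printed inputs, the standard baseline-adjusted formula and one follow-up, 36 clusters of 5 give about 65% power rather than 80%. This assumes two-sided testing, 1:1 allocation and no losses. About 51 clusters would be needed, or the detectable effect is about 0.36. One-sided testing narrows the gap to 76% and about 40 clusters but does not close it. What is established is the mismatch between the printed inputs and the printed result; its cause is not. Nor is it established that the trial is underpowered for whatever contrast is finally primary, since averaging over T1 to T3 would give about 0.84 to 0.86 before losses, provided that the mean effect is 0.3. Because the trial's size is justified by this one figure and correcting the text costs little, it should be corrected.

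**What to change.** Rewrite the sample size paragraph; no patients need be added.

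- Reconcile the result with the 0.5 cluster-level correlation, and state the sidedness, the allocation ratio, the formula and the number of follow-ups used.
- Give the power for a single-follow-up contrast as about 65%, with a detectable effect of about 0.36 (two-sided, 1:1).
- If the calculation did rely on an effect averaged over T1 to T3 in the planned mixed model, say so, give the between-visit correlations, and state that the effect is assumed to average 0.3 over the visits. Report power as about 0.84 to 0.86 before losses, and about 0.71 if the mean effect is 0.25.

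The cost is a few sentences and a less favourable power statement. Adopting the averaged contrast now, if it was not the original intention, would be more than rewording: it changes the estimand and should be decided on its merits, not to rescue the power figure. Adding the cluster-mean baseline as a covariate is optional; it raises single-visit power only from about 65% to 67%.

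### The 36 professionals and 180 patients needed for the analysis are also the numbers to be enrolled, so the stated 0.80 power assumes no loss and five patients in every cluster

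*Protocol article*

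**What the plan says.** The Sample size calculation closes with "With an alpha of 0.05, and a power of 0.80, 36 clusters (professionals) of 5 participants (patients) each are required" and sums this up as a "total of 36 professionals and 180 patients needed for the analysis". Its inputs are a standardised effect of 0.3 on the MANSA, an intracluster correlation of 0.10, and baseline to follow-up correlations of 0.5 (cluster level) and 0.8 (subject level).

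The abstract gives the same two figures as the enrolment plan: "36 professionals will be randomly allocated to either ICPT or CAU" and "180 Patients between 18–65 years of age will be included".

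The Design section schedules measurements at 6, 12 and 18 months. The Inclusion and exclusion criteria admit "Professionals who have an individual caseload of > 5 patients with a non-psychotic disorder", and ask that these professionals have not announced an intention to leave within 12 months. No readable section gives an expected loss, an inflation for it, or an allowance for unequal cluster sizes.

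**The concern.** A number needed for the analysis is a number with usable outcome data. A number to be included is a recruitment target. When the two are equal, the planned loss is zero. The article fixes both figures itself, so this is not a detail it leaves to a fuller protocol: if that document contains an allowance, one of the two statements is mislabelled.

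The fixed cluster size has a related weakness. The entry rule for professionals counts patients with a non-psychotic disorder. It does not count patients who also meet the age, care-use and exclusion criteria. Under Procedure, patients are approached only after their professional has joined, and they must then volunteer and consent. The rule therefore does not by itself secure five per professional.

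At stake is the 0.80 power for the primary outcome. If the analysed number falls below 180, or the clusters are uneven, the figure readers rely on is too high.

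**Working it through.** **Inputs.** From the Sample size calculation: alpha 0.05, power 0.80, effect size 0.3, ICC 0.10, subject-level correlation 0.8, cluster-level correlation 0.5, 36 clusters of 5. Assumed because not stated: a two-sided test, equal arms (18 professionals each), and all loss rates.

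**Reproducing 36 × 5.**
- Individually randomised total: 4 × ((1.960 + 0.842)/0.3)² = 348.8.
- Design effect for clusters of 5: 1 + (5 − 1) × 0.10 = 1.4.
- Baseline adjustment using the subject-level correlation alone: 1 − 0.8² = 0.36.
- Product: 348.8 × 1.4 × 0.36 = 175.8 patients, or 35.2 clusters, rounded up to 36. This gives 180 patients with no room for loss.

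This route leaves out the stated cluster-level correlation of 0.5. It is used here because it lands on the stated number, so the effect of loss can be seen with 180 taken at face value.

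**Power when fewer are analysed.** With k professionals per arm and m analysed patients each, SE = √(2 × [1 + (m − 1) × 0.10] × 0.36 / (k × m)), and power = Φ(0.3/SE − 1.960).

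| Assumed situation | k per arm | m | Analysed | SE | Power |
|---|---|---|---|---|---|
| No loss | 18 | 5 | 180 | 0.1058 | 0.81 |
| 10% of patients lost | 18 | 4.5 | 162 | 0.1095 | 0.78 |
| 20% of patients lost | 18 | 4 | 144 | 0.1140 | 0.75 |
| 30% of patients lost | 18 | 3.5 | 126 | 0.1195 | 0.71 |
| 2 professionals per arm lost with all their patients | 16 | 5 | 160 | 0.1122 | 0.76 |

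**Unequal clusters.** With a coefficient of variation CV of cluster size, the design effect becomes 1 + ((CV² + 1) × m − 1) × 0.10. For m = 5 and an assumed CV of 0.5 this is 1 + (1.25 × 5 − 1) × 0.10 = 1.525. Then SE = √(2 × 1.525 × 0.36/90) = 0.1105, and power is about 0.78 with all 180 retained.

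**Using every stated input.** The baseline correlation of the cluster means is r = (5 × 0.10 × 0.5 + 0.90 × 0.8)/1.4 = 0.693, and the factor is 1.4 × (1 − 0.693²) = 0.728. The requirement is then 348.8 × 0.728 = 253.9 patients, and 36 × 5 has power 0.65. With 20% patient loss this becomes 0.61. The gap between 0.80 and 0.65 involves no loss and is a separate question about the formula. The part due to 20% loss is about 0.05 here and about 0.06 on the route that reproduces 36 × 5.

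**Simple inflation, for scale.** 180/(1 − loss) gives 200 (10%), 225 (20%) and 258 (30%). This is slightly generous, because smaller analysed clusters carry a smaller design effect.

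**The case against.** The main objection concerns the analysis. The Statistical analyses section plans a linear mixed model on repeated measurements by intention to treat, so a patient seen at 6 or 12 months still contributes. The Sample size calculation names no visit. If the primary contrast were the mean of the three follow-ups, and the stated correlations held between all pairs of visits, power using all stated inputs would be 0.86 at five per cluster and 0.82 at four (0.79 with a t reference). On that reading 80% power roughly survives a 20% loss. This stands as a limit on the size of the problem. It does not remove the point, because neither section names an averaged contrast and the calculation speaks of a single follow-up measurement.

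A reader might infer more than the documents support:
- **That the stated power is certainly not delivered.** The averaged contrast shows otherwise, and no loss rate is given.
- **That discharge to a lower level of care is loss.** Under intention to treat it is an outcome, taken from administrative records, and such patients can still be measured.
- **That a departing professional takes the primary data along.** The MANSA is completed by the patient (Table 1), so the lost-professional row above is a pessimistic case. The entry criteria also guard against announced departures for the first 12 months.
- **That professionals will typically have only six candidates.** More than five is a floor. No cap of five patients is stated, so larger caseloads may offset smaller ones at the price of uneven clusters.

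The flow chart is not shown and may carry recruitment numbers. The point rests on the two text statements alone.

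**Conclusion.** The point holds in a moderate form. The enrolment figures equal the figures needed for the analysis, so 0.80 power is conditional on complete data at the analysed time point and on equal clusters of five. Rounding 35.2 clusters up to 36 leaves a margin of about 0.01, and 10% patient loss already takes power to 0.78. Over an assumed 10% to 30% loss, power runs from 0.78 to 0.71. Losing two professionals per arm with all their patients gives 0.76, and a cluster-size CV of 0.5 alone gives about 0.78.

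These figures assume a two-sided test, equal arms, one follow-up visit and complete loss of the missing patients. Partial data in the mixed model would make the fall smaller. The larger shortfall that appears when all stated inputs are used should not be attributed to missing patients.

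**What to change.** 1. Present 36 and 180 as recruitment targets, and state the expected analysed number separately.
2. State the assumed loss of patients and of professionals, and the visit or contrast to which the power refers.
3. Restate the power at the expected analysed number: for example about 0.75 at 144 patients (180 × 0.8), or lower if the sample size formula is also corrected.
4. Base the restated power on a realistic mean and variation of cluster size rather than a fixed five. No specific caseload threshold is needed.

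The cost is a rewritten paragraph and a power figure that may fall below 0.80. If the sponsor prefers to hold 0.80, the cost is more recruitment. At 20% loss, simple inflation of 180 means 225 patients, which is 45 professionals with five each before rounding to an even number. Keeping 36 professionals would need 225/36 = 6.25 patients each, so seven in practice (252 patients).

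### The 36 professionals and 180 patients needed for the analysis are also the numbers to be enrolled, so the stated 80% power allows for no loss to follow-up

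*Protocol article*

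**What the plan says.** The section on the sample size calculation bases the number on the MANSA. Its inputs are a standardised effect of 0.3 from the pilot study, an intra-cluster correlation of 0.10, and a baseline-to-follow-up correlation that "was set at 0.5 and 0.8 for cluster and subject level, respectively". It concludes: "With an alpha of 0.05, and a power of 0.80, 36 clusters (professionals) of 5 participants (patients) each are required". It then labels the result as the "total of 36 professionals and 180 patients needed for the analysis".

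The abstract (Methods/Design) uses the same figures for enrolment. It has 36 professionals being allocated, and "180 Patients between 18–65 years of age will be included".

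The Design section sets measurements at baseline and at 6, 12 and 18 months. The Statistical analyses section plans a linear mixed model on the repeated measurements, by intention to treat. The text gives no attrition rate, inflation factor or replacement rule. The only provision that bears on retention is that professionals must not have expressed an intention to leave within 12 months, which is 6 months short of the last measurement.

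**The concern.** A number labelled as needed for the analysis is a number of patients with usable outcome data. A number to be included is a count at entry. The two agree only if every patient enrolled supplies the follow-up data that the calculation assumes.

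The article gives some reason to expect that they will not. Follow-up runs for 18 months, the target population may be passed between services, and discharge to a lower level of care is itself one of the study's aims. If some patients give no follow-up MANSA, the 80% no longer describes the trial, and a null result on quality of life would be read against a somewhat overstated power.

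**Working it through.** **Inputs.** From the sample size section: alpha 0.05, power 0.80, effect 0.3, ICC 0.10, correlations 0.5 (cluster) and 0.8 (subject), and 36 clusters of 5. Assumed here, because the article does not state them: a two-sided test, 1:1 allocation, and the retention rate.

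**Step 1: reproduce 180.** Without clustering or baseline adjustment, the number per arm is 2 × (1.960 + 0.842)² / 0.3² = 174.4. The design effect for clusters of 5 is 1 + 4 × 0.10 = 1.4. A factor for baseline adjustment remains, and the article does not name its formula. Three candidates:

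- (a) Subject-level correlation only: factor 1 − 0.8² = 0.36. Total 2 × 174.4 × 1.4 × 0.36 = 175.8, rounded up to 36 clusters, or 180 patients.
- (b) Both correlations, mean of two follow-ups: r = (5 × 0.10 × 0.5 + 0.90 × 0.8) / 1.4 = 0.693, factor (1 + r)/2 − r² = 0.366. Total 178.9, again 36 clusters, or 180 patients. This takes the correlation between the two follow-ups as also r.
- (c) Both correlations, one follow-up: factor 1 − r² = 0.520. Total 253.9, or 52 clusters. This does not reproduce the plan.

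So 180 follows from (a) or (b), and neither contains a loss term. Rounding up to whole clusters leaves little margin: power falls below 80% at a patient loss of about 3.6% under (a) and 1.3% under (b).

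**Step 2: power if 180 are enrolled and some give no follow-up.** With k = 36 professionals and m patients observed per professional, the variance of the standardised effect is

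Var = 4/(k·m) × [1 + (m − 1) × 0.10] × factor, and power = Φ(0.3/√Var − 1.96).

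Under (b), r and the factor are recalculated at each m.

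| Complete loss (assumed) | Patients observed | m | Power (a) | Power (b) |
|---|---|---|---|---|
| 0% | 180 | 5 | 80.9% | 80.2% |
| 5% | 171 | 4.75 | 79.6% | 79.3% |
| 10% | 162 | 4.5 | 78.2% | 78.2% |
| 20% | 144 | 4 | 74.9% | 75.7% |
| 30% | 126 | 3.5 | 70.9% | 72.7% |

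For example, under (a) at 20% loss: Var = 4/144 × 1.3 × 0.36 = 0.0130, 0.3/√0.0130 = 2.631, and Φ(2.631 − 1.96) = 74.9%. The fall is modest because smaller clusters also have a smaller design effect (1.3 in place of 1.4).

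**Step 3: does the result hang on the formula?** Take the stated 80% as the base and use only the variance ratios from (c): 1.051, 1.114 and 1.196 at m = 4.5, 4 and 3.5. Then Φ(2.802/√ratio − 1.96) gives 78.0%, 75.6% and 72.7%. The relative loss is much the same. Formula (c) cannot serve as the base itself, since it gives 65.5% at 36 × 5.

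**Step 4: enrolment that would leave 180.** 180/(1 − loss) is 200 at 10%, 225 at 20% and 258 at 30%. This is for scale only.

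**The case against.** The case on the other side has several parts, and some of it stands.

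- *A condensed article may leave attrition to the full protocol, and the enrolment figure comes from the abstract.* The flow chart is not shown either, and professionals with more than five suitable patients could enrol more. This would answer a complaint that an attrition sentence is missing. It does not answer two printed statements that give the same number for analysis and for inclusion.
- *The mixed model uses partial follow-up.* This stands. A patient seen at 6 months but not later still contributes, so the complete-loss figures are upper bounds for such patients. The model recovers little or nothing for a patient with no follow-up MANSA.
- *The article names no single primary time point.* This stands. If the effect is averaged over all three follow-ups (assuming the same correlation between follow-ups as with baseline), the factor is (1 + 2r)/3 − r² = 0.315. Power is then 85.8% at 36 × 5, 83.9% at 90% retention and 81.6% at 80%.

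A reader might therefore infer too much: that the 80% holds only if nobody is lost, or that the trial never had it. The documents do not support that, because they fix neither the retention nor the visits on which the effect is estimated. A reader might also count each departing professional as five lost patients. The MANSA is completed by patients and the analysis is by intention to treat, so a professional's departure need not remove primary outcome data. Nor does the article describe the population as suicidal: it says only that suicidal patients may take part.

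**Conclusion.** The point holds as an inconsistency between two stated numbers. The 80% belongs to 180 patients with the follow-up data that the calculation assumes, whereas 180 is the number to be enrolled, with no allowance between them. The calculation of 180 is not itself shown to be wrong, since two standard formulas reproduce it.

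From the stated 80%, complete loss of 10%, 20% or 30% of patients would give about 78%, 75–76% or 71–73%. This rests on assumed loss rates, a two-sided test, equal allocation and losses spread evenly over professionals. The true reduction would be smaller where patients miss only some visits, and it depends on which follow-ups define the treatment effect. At 5–10% loss it is only about 1–3 points. The correction is worth making because it is cheap and concerns a figure against which the result will be read.

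**What to change.** In the abstract and in the sample size section, separate the number enrolled from the number analysed. Keep 36 × 5 = 180 as the enrolment. State the retention expected at the time point, or points, on which the primary comparison rests, and the number of patients then analysed. Restate the power for that number: for example, at 80% retention, 144 patients analysed (about 4 per professional) and power of about 75–76%. State which follow-ups the calculation used, because the figure depends on it.

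This costs a sentence or two. It needs no extra patients and no change to the design or the analysis. The only downside is a slightly less favourable stated power.
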